### Statistics and data analysis

#### Sample size and power calculation

The sample size estimation was performed by the study statistician for a stepped wedge cluster randomised design using STATA release 14 [34]. With 11 centres (clusters) participating and an intra cluster correlation (ICC) of 0.0026 a minimum sample size of 47,916 pregnant women (23,958 before change and 23,958 after change of the new GDM criteria) have 90% statistical power with a 5% significance level to detect an absolute reduction in LGA by 1.5% on a population level (from the existing 10 to 8.5%). ICC was estimated from the variation in LGA incidence in year 2012 between participating centres which varied between 7.7 and 13.3% (0.077–0.133). Assuming that the variation in LGA incidence between centres follows a normal distribution, the variation in LGA incidence were estimated as mean 0.1067 and standard deviation (SD) 0.0164. The coefficient of variation (CV) is 0.154 (SD divided by the mean) and the CV can be expressed as an ICC.

The total estimated number of inclusions (=births) during the inclusion period for the participating centres is approximately 65,000. It is not possible to predict the exact number of births during the study due to the differences in sizes of the centres. Some incompleteness (estimated 10%) of data on maternal characteristics (mainly BMI) is expected. The calculation indicates that there will be sufficient power for the main outcome measure (LGA) even if 1–2 centres would drop out.

The proposed statistical analysis methods for stepped wedge designs will be used including Generalized Estimating Equation (GEE) models or mixed effect logistic models to evaluate the primary outcome, LGA. Mixed effect logistic models will include centres as random effects, which is the cluster and the randomisation unit in this design, and the intervention and time periods as fixed effects, or time as a random effect [35]. Adjustment for time is to compensate for calendar time changes over time in LGA incidences that are not due to the intervention changing from the old to new GDM criteria, but because of potential temporal trends in LGA incidence.

As the randomisation is on the cluster level and not on the participant level, we will adjust for important prognostic predictors for LGA, such as chronic hypertension, mother’s age, BMI, country of mother’s birth and the mother’s smoking behaviour during pregnancy. Stratification with interaction tests by prognostic factors will be used to further investigate if the associations with LGA between the two diagnostic criteria are heterogeneous and the new diagnostic criteria have an even larger impact in some subgroups according to risk factors.

Because of the stepped wedge study design, some recommended design-specific analyses will be conducted such as stratification by time period to evaluate if the intervention association with outcomes are homogenous during the study time period, or heterogeneity within centres between the two interventions. The secondary adverse neonatal and maternal outcomes will be analysed using the same type of methods and considerations as for the primary outcome. A sub-analysis will be conducted comparing those with fasting glucose 5.1–6.9 mmol/L and/or 2-h glucose 8.5–8.9 mmol/L before and after the switch in criteria.

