#### Randomisation

As the expected number of births varies across the participating centres, a stratified randomisation by centre size was conducted using two strata. The first strata was the two largest populated study centres (Stockholm and Gothenburg) which was randomised to change GDM criteria in June or August of 2018. The second strata with the nine remaining centres was changing, one centre per month, in a randomised order from February to July and September to November of 2018. The randomisation allocation was performed using computer-generated, random allocation sequences using SPSS version 22 (Armonk, NY:IBM Corp) by the study statistician at Clinical Epidemiology and Biostatistics, Region Örebro County. The randomisation was concealed from the participating centre and the list is stored in a safe at Örebro University Hospital.

The study statistician provided information on the randomisation to the study coordinator who in turn informed the relevant centre through the local PI, 2 months prior to when the centre being randomised to using the new GDM criteria. Staff at all sites were blinded until informed by their local PI of their start date to change from the *control period* (old GDM criteria) to the *intervention period (*new GDM criteria*)*.

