#### Procedures

A 3-month *national preparation period* was organized between October to December 2017 (Fig. 2), for all sites to consolidate their local approach to screening, changing diagnostic testing to venous sampling, modifying and consolidating the agreed approach to GDM treatment and the agreed approach to obstetric management.

The trial started on the 1st of January 2018 with 1 month of baseline data collection when no randomisation occurred. Subsequently, at periodic time points called “steps”, sites changed to the new GDM criteria in a randomised order over a 10 months period. In December 2018 all sites used the new criteria. The last birth is expected in August 2019.

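### The 47,916-woman minimum for 90% power fits 11 equal centres; with the plan's own centre sizes and switch schedule it gives about 81%, and 90% needs about 64,000

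*Protocol article*

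**What the plan says.** Under Sample size and power calculation, the article gives "a minimum sample size of 47,916 pregnant women (23,958 before change and 23,958 after change of the new GDM criteria) have 90% statistical power". The inputs are stated: "With 11 centres (clusters) participating and an intra cluster correlation (ICC) of 0.0026", "with a 5% significance level to detect an absolute reduction in LGA by 1.5% on a population level", with the rate falling "from the existing 10 to 8.5" percent. The ICC comes from variation between centres: "The coefficient of variation (CV) is 0.154 (SD divided by the mean) and the CV can be expressed as an ICC".

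The same section expects more births than this minimum: "The total estimated number of inclusions (=births) during the inclusion period for the participating centres is approximately 65,000". It anticipates about 10% incomplete data on maternal characteristics, mainly BMI. It concludes that power for LGA would be sufficient even with the loss of one or two centres.

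The Randomisation section recognises that centres differ in size: "As the expected number of births varies across the participating centres, a stratified randomisation by centre size was conducted using two strata". The two largest centres take June and August 2018. The other nine switch one per month in February to July and September to November. The Procedures section confirms that "sites changed to the new GDM criteria in a randomised order over a 10 months period", after a January baseline and with all centres switched in December.

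**The concern.** The before and after numbers are exactly equal, and 47,916 divides exactly into 11 centres x 12 months x 363 women. Both point to a layout of 11 equal centres and 11 single-centre steps. The trial described elsewhere in the article is not that layout, and the power section mentions no allowance for unequal centre size.

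Two statements depend on the figure. One is the implied reserve of 65,000 - 47,916 = 17,084 women. The other is the reassurance about losing one or two centres. If the minimum is too low, both mislead, and a null result could later be read against a margin that was not there.

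**Working it through.** **Inputs.** From Sample size and power calculation: 11 clusters, ICC 0.0026, rates 0.10 and 0.085, significance level 5%. Two-sided testing is assumed because the article does not say; it reproduces the stated figure. From Table 1, births in 2017: 28,602; 3,565; 3,120; 3,232; 4,200; 9,550; 538; 4,446; 4,944; 3,703; 2,085 (sum 67,985). From Randomisation and Procedures: 12 monthly periods and the switch months above.

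**Model.** Generalised least squares variance of the intervention effect (Hussey-Hughes), with a random centre effect and fixed period effects, as in the article's mixed model but on the linear scale. Births are spread evenly over months within a centre. Power = Φ(0.015/SE - 1.96).

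**Step 1: reproduce the stated figure.** Eleven equal centres, 11 steps, 12 periods, m = 363 per centre-month.
- s² = 0.10 x 0.90/363 = 0.0002479
- τ² = 0.09 x 0.0026/(1 - 0.0026) = 0.0002346
- U = 66 intervention centre-months. W and V, the sums of squared intervention counts by period and by centre, are both 506.
- Variance = 11s²(s² + 12τ²) / [(11U - W)s² + (U² + 132U - 12W - 11V)τ²] = 11s²(s² + 12τ²) / [220s² + 1,430τ²] = 0.00002142
- SE = 0.004628; 0.015/0.004628 = 3.241; power = Φ(1.281) = 89.99%

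This layout has 66 control and 66 intervention centre-months, and 66 x 363 = 23,958, the stated split.

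**Step 2: the design described.** Control months per centre are 1 to 6 and 8 to 10 for the nine smaller centres (21 + 27 = 48) and 5 and 7 for the two largest (12). The split is therefore 60:72. The largest centre holds 28,602/67,985 = 42% of births, and the two largest hold 38,152/67,985 = 56%. The share of women in the control period averages about 47.5% and ranges from about 42% to 53% by allocation.

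**Step 3: power at 47,916**, same ICC and variance, averaged over random permitted allocations:

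| Centre sizes | Schedule | Power |
|---|---|---|
| Equal | 11 single steps | 90.0% |
| Equal | actual 10 months | 88.3% |
| Table 1 | 11 single steps, random order | about 85% |
| Table 1 | actual 10 months, stratified | 80.6% (76.2-83.7%) |

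In the last row the average SE is about 0.0053: 0.015/0.0053 - 1.96 = 0.87, or about 81%. No sampled allocation reached 90%.

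**Step 4: other sample sizes and variances**, Table 1 sizes and actual schedule:

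| Variance | 47,916 | 65,000 | N for 90% |
|---|---|---|---|
| 0.10 x 0.90 = 0.0900 | 80.6% | 90.3% | about 64,000 |
| mean of 0.10 x 0.90 and 0.085 x 0.915 = 0.0839 | 83.2% | 92.2% | about 60,000 |
| 0.1067 x 0.8933 = 0.0953 | 78.3% | 88.7% | about 68,000 |

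With variance 0.0900 and assumed ICCs from 0.0005 to 0.01, power at 47,916 runs from 85% down to 79%.

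**Step 5: losses from 65,000 births**, variance 0.0900. Power is 78% without the largest centre, 85% without the second largest, 69% without both, 88% without the two smallest, and just under 90% without the 538-birth centre alone. If the BMI-adjusted analysis used complete cases only and lost 10% of women (58,500), power would be about 87%.

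**The case against.** The strongest reply is that 47,916 is a minimum and not the planned number. The trial takes all births in the participating centres, and the expected 65,000 still give about 90%. That stands. A reader might infer that the trial is underpowered as planned; the documents do not support this.

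Nor do they establish that the expected 10% incompleteness takes the trial below its target. That incompleteness concerns adjustment covariates, not LGA, and the article does not say the analysis is complete-case. The 87% is conditional on that assumption.

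It is also fair that the article does not define sufficient power as 90%. Losing any one of the nine smaller centres leaves about 86-90%, and losing any two of them about 82-88%. The 90% margin goes, but power does not collapse unless the largest centre is lost.

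Equal sizes are an inference, though the factorisation, the split and the power all agree. It would be too simple to blame unequal sizes for most of the loss. With the schedule changed first, sizes account for about 8 points. With sizes changed first, they account for about 5, and the schedule, with both large centres switching mid-year, for almost as much again.

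Finally, correlation within a centre that decays over months would lower power further, but the article gives no such parameter. That is not part of this error.

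**Conclusion.** The concern holds as an error in a stated figure. Under the article's own centre sizes and schedule, 47,916 women give about 81% power (76-84% by allocation; mean 78-83% across variance choices from the plan's own rates), not 90%. About 64,000 (60,000-68,000) are needed. The fixed equal split does not describe this design, and the statement about losing one or two centres needs qualifying. At the expected 65,000 births power is about 90% (89-92%), so the target is met with almost no reserve.

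These figures rest on the linear mixed-model approximation, a two-sided test, 2017 size proportions, even monthly births, and a centre correlation that is constant over time.

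**What to change.** Recompute power with the Table 1 sizes and the actual switch schedule, and name the variance used. Replace the 47,916 statement with: about 64,000 women (60,000-68,000) for 90% power; about 81% at 47,916; about 90% (89-92%) at the expected 65,000. Delete the 23,958/23,958 split. Qualify the drop-out sentence by naming the losses and the remaining power: 78% without the largest centre, 85% without the second largest, 69% without both, 88% without the two smallest. If complete-case adjustment is intended, add the 87%. A sensitivity analysis with within-centre correlation decaying over time is optional.

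The cost is one recalculation and a reworded paragraph. Enrolment, design and analysis stay as they are; the only downside is a less favourable stated figure.

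### The assurance that power survives the loss of one or two centres is not true of Stockholm, which supplies 42% of births

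*Protocol article*

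**What the plan says.** The section on sample size and power specifies "With 11 centres (clusters) participating and an intra cluster correlation (ICC) of 0.0026" and gives "a minimum sample size of 47,916 pregnant women (23,958 before change and 23,958 after change of the new GDM criteria"). These numbers are said to "have 90% statistical power with a 5% significance level to detect an absolute reduction in LGA by 1.5% on a population level", that is "from the existing 10 to 8.5"%. On expected recruitment it says: "The total estimated number of inclusions (=births) during the inclusion period for the participating centres is approximately 65,000". It then concludes: "The calculation indicates that there will be sufficient power for the main outcome measure (LGA) even if 1–2 centres would drop out".

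The same section acknowledges that centres differ in size, but only to explain why the number of births cannot be predicted exactly. The Randomisation section acts on the difference: "The first strata was the two largest populated study centres (Stockholm and Gothenburg") and was kept apart from the nine smaller centres. Table 1 lists births per centre for 2017, from 538 in Gotland to 28,602 in Stockholm.

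**The concern.** The drop-out sentence treats the centres as interchangeable. The expected surplus is 65,000 − 47,916 = 17,084 women. An average centre would contribute 65,000 / 11 ≈ 5,909, so the surplus looks like room for two centres to leave. Stockholm alone is larger than the whole surplus.

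This is the article's only statement on losing a cluster. A steering group relying on it could accept the loss of the largest centre's data and still read a null LGA result as adequately powered.

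**Working it through.** **1. Reproducing the plan's figure.** Inputs from the sample size section: 11 clusters, ICC 0.0026, LGA 10% against 8.5%, 5% significance (taken as two-sided), 90% power. From the design: 12 monthly periods. The Hussey-Hughes model has a random centre intercept and fixed period effects.

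- Total variance 0.10 × 0.90 = 0.09; between-centre τ² = 0.09 × 0.0026 = 0.000234; within-centre σ² = 0.09 × 0.9974 = 0.089766.
- For centre i with n_i women per month, V_i = (σ²/n_i)·I + τ²·J, where I is the identity matrix and J the matrix of ones. Var(effect) is the treatment element of (Σ X_i′V_i⁻¹X_i)⁻¹.
- Power = Φ(0.015 / SE − 1.96).

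With 11 equal centres, one switching at each step, the smallest cell reaching 90% is 363 women (power 0.9007). 11 × 12 × 363 = 47,916, the stated minimum exactly. The plan's calculation therefore assumes centres of equal size.

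**2. Head count, with no model.** Table 1 births sum to 67,985. Scaling to the expected 65,000 multiplies each centre by 65,000 / 67,985 = 0.9561.

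| Lost | 2017 births left | Scaled to 65,000 | Against 47,916 |
|---|---|---|---|
| Stockholm | 39,383 | 37,654 | below by 10,262 (21%) |
| Stockholm and Göteborg | 29,833 | 28,523 | below |
| Göteborg | 58,435 | 55,869 | above |
| Göteborg and Malmö (largest pair without Stockholm) | 53,491 | 51,142 | above |
| Gotland | 67,447 | 64,486 | above |

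Ten of 11 single losses and 45 of 55 double losses stay above the minimum. The 10 failing pairs are exactly those with Stockholm. Stockholm's loss also fails on unscaled 2017 births (39,383).

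**3. Power with actual centre sizes.** The same model was run with Table 1 sizes scaled to 65,000, births even over 12 months, Stockholm and Göteborg switching in June or August, and the other nine in random order over February–July and September–November. Results are averages over randomly drawn switch orders.

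| Centres lost | Variance at 10% (0.09) | Variance at the mean rate (0.0925 × 0.9075) |
|---|---|---|
| None | 0.904 | 0.923 |
| Stockholm | 0.781 (0.742–0.807 over orders) | 0.809 |
| Göteborg | 0.847 | 0.871 |
| Stockholm and Göteborg | 0.69 | 0.72 |
| Any one of the other nine | 0.865 (Malmö) to 0.899 (Gotland) | 0.887 (Malmö) to 0.918 (Gotland) |

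The first variance is the one that reproduces 47,916.

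**The case against.** The strongest defence is that the sentence reports what the stated calculation indicates, and that calculation has equal centres. On that model with 65,000 women (about 492 per cell), power is 0.941–0.948 after any single loss and 0.904–0.925 after any double loss. This stands as an account of where the sentence came from. It does not make the sentence true of this trial, whose centres range from 538 to 28,602 births.

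A second defence is that sufficient is never defined for the drop-out case; 90% is attached only to the minimum sample size. Against 80%, every single loss except Stockholm's is comfortably sufficient on average, and Stockholm's gives 78% or 81% depending on the variance. That softens the criticism of a Stockholm loss alone. It does not help for Stockholm with Göteborg, at 69–72%.

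Third, LGA comes from the national pregnancy register, so a centre that stops cooperating need not lose its data, and the article reports that all sites were using the new criteria in December 2018. Both points reduce the practical risk. The sentence remains wrong as a stated property of the design.

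A reader might go further and infer that no loss of one or two centres keeps 90% power. The documents do not support that. Losing Gotland averages 0.899 and reaches 0.90 in about half of the switch orders. With mean-rate variance, losing Gotland (0.918), Kristianstad (0.908) or both (0.903) keeps 90% on average. A reader might also deduct the expected 10% incompleteness and work from 58,500 women. The article confines that incompleteness to maternal characteristics, mainly BMI, and does not say that the primary analysis uses complete cases only.

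**Conclusion.** The unqualified assurance is incorrect for Stockholm. Losing that centre's data leaves about 37,650 women against a stated minimum of 47,916 and about 78% power (81% with mean-rate variance); losing Göteborg as well leaves about 69% (72%). The head-count part rests only on the article's own figures and on splitting 65,000 in proportion to 2017 births.

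For the other centres the sentence passes on head count, but 47,916 was derived for 11 equal centres. With actual sizes the full trial averages only about 90%, so most other losses have little or no margin above that level. The power figures assume a constant ICC of 0.0026 without decay over time, even monthly births and averaging over switch orders.

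**What to change.** Replace the drop-out sentence with one that names the exception, for example:

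> The minimum of 47,916 is still met if one or two centres other than Stockholm drop out; loss of Stockholm would leave about 37,650 women and about 78% power. Because centre sizes are very unequal, there is little or no margin above 90% for most other losses.

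State the assumptions beside it: total variance 0.09, ICC 0.0026, Table 1 sizes scaled to 65,000 births spread evenly over 12 months, and an average over the switch orders that the randomisation allows. The new text should not claim that 90% power is lost whenever any centre leaves.

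The cost is wording only: no additional women, data or analyses, though the stated assurance becomes less favourable.

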### SW-CRCT: strengths and limitations

The stepped wedge randomised controlled design is particularly beneficial when the intervention is likely to do more good than harm and is mainly used to evaluate routine implementation, as is the case for the CDC4G trial. The design is practical where it is not possible to deliver the intervention to all the participants at the same time for logistical, practical or financial reasons. The stepped wedge design is also appropriate for cost-effectiveness analysis of an intervention on a population basis (i.e. when changes across a whole population/service occur), also making it suitable for the CD4G study.

Disadvantages of the stepped wedge design are difficulties in blinding the participants and those delivering the intervention since the step from control to intervention is evident for both. It is also important to note that the stepped wedge design is likely to lead to a longer trial duration than a traditional parallel design, particularly where effectiveness is measured immediately after implementation. Since the implementation of the new criteria is expected to do more good than harm and is going to continue after the study period there are no real disadvantages from the participant’s point of view. Step-wedge trials can be impacted upon by wider secular trends that can differ between the beginning and end of the study period. In CDC4G, the design has included an alignment, and run in, of all significant clinical policies before the trial commenced, and a clear directive not to introduce any service changes during the study period. A major limitation in cluster randomised trials is the need for larger numbers to overcome the ICC.

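### The primary model may treat time as random instead of fixed, which in this one-way roll-out lets part of any secular LGA trend, up or down, enter the intervention estimate

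*Protocol article*

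**What the plan says.** The analysis text stands in the protocol article under *Sample size and power calculation*. It names "Generalized Estimating Equation (GEE) models or mixed effect logistic models to evaluate the primary outcome, LGA". For the mixed model, centre is a random effect, "and the intervention and time periods as fixed effects, or time as a random effect". No order of preference is given. The next sentence states the purpose: "Adjustment for time is to compensate for calendar time changes over time in LGA incidences that are not due to the intervention".

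*Randomisation* and *Procedures* set a one-way schedule. All centres are on the old criteria in January 2018. The nine smaller centres switch one per month in February–July and September–November, and the two largest switch in June or August. All are on the new criteria in December. Under *SW-CRCT: strengths and limitations* the article accepts the risk: "Step-wedge trials can be impacted upon by wider secular trends that can differ between the beginning and end of the study period".

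The sample size reads: "With 11 centres (clusters) participating and an intra cluster correlation (ICC) of 0.0026 a minimum sample size of 47,916 pregnant women", said to "have 90% statistical power with a 5% significance level to detect an absolute reduction in LGA by 1.5% on a population level", that is "from the existing 10 to 8.5" percent.

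**The concern.** In a stepped wedge, the time term separates the effect of the new criteria from whatever else changed over the year. Fixed periods do this without any assumption about the shape of the trend. A random month intercept behaves differently. Its effects come from a zero-mean distribution, so they are pulled towards no trend, and they are assumed unrelated to exposure. Here exposure rises with the calendar under every permitted randomisation order, so that assumption fails. The part of the trend that is shrunk away is attributed to the intervention.

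The wording offers random time as an alternative to fixed periods, not as an addition. An analyst could therefore follow the protocol and still report drift in LGA as benefit, or have drift conceal a benefit.

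**Working it through.** **1. The plan's own figure.** Inputs from the sample size section: 11 centres, ICC 0.0026, LGA 10% against 8.5%, N = 47,916. Assumed: two-sided 5%, 12 monthly periods, one centre switching per step, equal sizes.

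- Centre-months: 11 × 12 = 132; women per centre-month: 47,916 / 132 = 363 exactly.
- ICC: the plan has the LGA incidence "estimated as mean 0.1067 and standard deviation (SD) 0.0164", so CV = 0.0164 / 0.1067 = 0.154; at 10%, (0.154 × 0.10)² / 0.09 = 0.0026.
- Hussey–Hughes variance with **fixed** periods: I·s²(s² + T·c²) / [(I·U − W)s² + (U² + I·T·U − T·W − I·V)c²].
- Here I = 11, T = 12, U = 66, W = V = 506, s² = 0.09/363 = 0.0002479, c² = 0.0026 × 0.09/0.9974 = 0.0002346.
- Denominator: 220 × 0.0002479 + 1430 × 0.0002346 = 0.390. Numerator: 8.354 × 10⁻⁶. SE = 0.00463.
- Power: Φ(0.015/0.00463 − 1.96) = 0.8999.

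The stated 90% is reproduced, and by a model with fixed periods.

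**2. Exposure against month.** Under the actual schedule the number of centres on the new criteria, January to December, is 0, 1, 2, 3, 4, 6, 7, 8, 9, 10, 11, 11 (with June and August for the two large centres). The correlation of exposure with month is 0.68 unweighted and 0.76–0.77 weighted by Table 1 births.

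**3. Expected leakage, closed form.** The estimator is (Z′V⁻¹Z)⁻¹Z′V⁻¹y with V = diag(σ²/n) + 0.0154²·CC′ + τ²·PP′. Z holds exposure and an intercept; C and P are centre and month indicators; y is a linear trend; τ is the actual SD of the month effects (0.328 × trend). Sizes are Table 1 births / 12, averaged over 200 permitted schedules.

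| Assumed change over 2018 (points) | Share leaked, random month | Shift (points) |
|---|---|---|
| 0.5 | 51% | 0.26 |
| 1.0 | 44% | 0.44 |
| 1.5 | 36% | 0.55 |
| 3.0 | 18% | 0.55 |

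With no time term at all the share is 54%.

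**4. Simulation with the month variance estimated.** True effect zero, Table 1 sizes (as given or scaled to 65,000), the actual schedule, 150 to 600 runs per trend. Ranges are across sets of runs.

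| Assumed trend (points) | Random month: mean estimate | False positives |
|---|---|---|
| 0 | – | 2% |
| −0.2 | −0.11 | 8.5% |
| −0.5 | −0.24 to −0.27 | 15–20% |
| −1.0 | −0.48 to −0.52 | 46–51% |
| −1.5 | about −0.7 | 72–74% |
| +1.0 | +0.47 to +0.49 | – |

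For trends of 0.5 to 1.5 points the month variance was estimated as zero in 33–48% of runs, which leaves no time adjustment. With fixed months the mean stayed within 0.07 points of zero and false positives were 3–9%, consistent with 5% given simulation error.

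**5. Where the excess rejections come from.** With no trend, the random-month model SE was 0.264 points and the empirical SD 0.253–0.257. At −0.5 the two were 0.264 and 0.268. A shift of 0.25 with SE 0.264 predicts rejection of Φ(−1.96 + 0.95) + Φ(−1.96 − 0.95) = 16%. A shift of 0.5 predicts Φ(−1.96 + 1.89) = 47%. Both agree with the table, so bias alone accounts for the excess.

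**The case against.** - **Fixed periods are named first, and choosing among models can be left to the analysis plan.** True, and the sample size matches fixed periods. But the article does more than leave the choice open. It names an option that works against the purpose given in the next sentence.
- **The random term may mean variation of periods within centres.** Added to fixed periods, such a term would not cause this bias. The sentence, however, sets random time against fixed periods. The fix keeps the harmless meaning.
- **The plan has other safeguards.** Covariate adjustment (age, BMI, country of birth, smoking, chronic hypertension) would remove drift carried by those factors. The GEE route is not touched by a criticism of random month effects. Stratification by time period gives a check. Policies were aligned and frozen. All of this stands as mitigation and makes the sizes illustrative. None of it withdraws the option or removes drift from other causes.
- **The trend is assumed.** Correct. The documents speak only of potential trends, and a 1.0-point fall is 10% of the baseline rate. At 0.2 points the distortion is modest.

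Three stronger inferences are tempting and fail. A reader might take the smaller standard error under random time (0.26 against 0.46 points) as falsely small. With no trend it matches the sampling spread, so it reflects efficiency under an assumption. A reader might also infer that the option favours the new criteria. The shift follows the sign of the trend, and the documents give no direction. Nor is a constant fraction leaked: the share falls as the trend grows.

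**Conclusion.** The point holds. If the random option replaces fixed periods and LGA drifts over 2018, the primary estimate is biased in the direction of the drift. The size is about 0.25 points for an assumed 0.5-point change and about 0.5 points for a 1.0-point change, the latter a third of the 1.5-point target. False positives rise to 15–20% and 46–51%.

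These figures rest on an assumed linear trend, no true effect, a month intercept crossed with centre, and a linear approximation to the logistic model without covariates. They show what the wording permits; they do not predict this trial's result. It cannot be said that the random option will be used or that a trend exists.

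**What to change.** In the analysis paragraph, remove random time as a substitute for fixed periods. State that calendar period enters the primary LGA model as a fixed categorical effect, and the secondary models likewise where event counts allow. For very rare outcomes in Table 2, such as Erb's palsy or neonatal death, twelve monthly categories may cause separation or non-convergence; keep time fixed there in a coarser or parametric form. If random variation over time is wanted, specify it as a centre-by-period effect in addition to the fixed periods.

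The cost is a short edit and 11 parameters on about 65,000 women. The standard error rises from about 0.26 to about 0.46 points. That is the precision of the fixed-period model behind the stated sample size: 1.5 / 0.46 = 3.26, and Φ(3.26 − 1.96) = 0.90, so the planned power is not lost.
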